### Telehealth Monitoring Platform

The exercise intensity is prescribed at a moderate-to-vigorous intensity level, which is monitored through a web-based platform with physiologic devices to support remote telehealth supervision of the intervention. The platform, referred to as TeleRehab, includes an Android (Google LLC) app that is installed on a computer tablet with Bluetooth capability (Samsung FE S7, Samsung USA), which sends data and allows 2-way communications to a secure web server. HR data are recorded and transmitted for real-time viewing by both the user and research staff using an optic HR sensor (Polar Verity Sense, Polar). The device instructions from the manufacturer state that the sensor can be worn on the head, forearm, or upper arm. For the M2M-C exercise intervention, the HR sensor is placed on a thin, elastic sports headband and worn on the temple of the head. Based on internal testing among research staff (nonpublished findings), the head placement resulted in more accurate readings during intervention exercise than when the device was worn on the forearm or upper arm. The head placement avoided signal disruption caused by the rapid and consistent arm movements required for the exercise intervention. At the end of each session, the platform provides the summary of exercise minutes (ie, light or moderate-to-vigorous) based on the predetermined HR zone. For participants with blunted HR, RPE is used. The TeleRehab app was an upgraded version of one used previously in a tele-monitored feasibility exercise study among people with SCI [51].

### Control Arm—Home-Based, Asynchronous Standard Exercise Training

For ethical and engagement purposes, the control group receives access to a YouTube playlist of standard exercise training (SET) videos adapted for people with physical disabilities. They are advised a similar prescription as the intervention group of 3 exercise sessions per week. The SET program is based on the National Center on Health, Physical Activity, and Disability 14-Weeks to a Healthier You program launched in 2008. It involves various exercises that are performed in both standing and seated positions, including the upper and lower extremity range of motion (2 videos, 5 min each), muscle strength (3 videos, 5 min each), aerobic fitness (1 video, 5 min; 2 videos, 10 min each), balance (1 video, 2 min; 2 videos, 5 min each), and a cool down (1 video, 5 min) [52].

### Procedure

This study’s procedure is administered by a project coordinator with oversight by the principal investigator (PI) and coinvestigators and monitored through a fidelity monitoring plan. Our intervention fidelity plan is based on the best practices and recommendations from the Behavior Change Consortium [26]. These recommendations are intended to link theory and application across 5 primary study phases, including study design, provider training, monitoring and improving the delivery of the intervention, and monitoring and improving the enactment of intervention skills.

The project coordinator, who is specific to participant engagement, contacts interested participants via telephone, describes this study and its requirements, and conducts the screening based on this study’s inclusion and exclusion criteria. For eligible individuals, the project coordinator then obtains physician approval. Upon approval by the physician, the project coordinator then distributes the informed consent document electronically as a final step in enrollment. After completing the informed consent, a baseline self-report questionnaire packet and a current medication list form are sent electronically. The project coordinator follows up with a telephone call to schedule a baseline data collection visit and provide verbal and written instructions regarding the baseline testing procedure, completion of the questionnaire packet and medication list, and directions with parking information. The project coordinator contacts the participant by telephone 24 hours before the appointment as a reminder. Upon arrival at the adaptive human performance laboratory, the project coordinator reviews this study’s procedures with the participant and then initiates the baseline data collection. The baseline data collection is undertaken by treatment-anonymous research staff who will administer the second level of eligibility screening based on CMH indicators. The eligible participant then undertakes a series of physiological tests, and the composition of those measures takes approximately 2 hours.

Once the baseline assessment is completed, participants are randomly assigned to either the intervention or control conditions using a random numbers sequence with concealed allocation. The project coordinator unfolds the allocation information via this study’s database, communicates the condition of assignment with the participant and, if allocated to the M2M-C intervention, prepares the necessary equipment for program participation. The participant will also meet with instructors and assistant telecoaches. If allocated to the control condition (SET), the project coordinator prepares the tablet with access to the SET videos. Lastly, the project coordinator will schedule a goal-setting session to be completed within 2 weeks between the participant and PI. This is carried out for both groups.

Participants in both intervention and control groups receive a 15-minute, individual goal-setting session at each time point from the PI, who is trained in physical activity counseling. They discuss participant’s outcome expectations from the program and review the goal of the program based on the given exercise prescription. The participants are prompted to share any foreseen barriers to complying with the program and guided to develop a relapse prevention plan (eg, identifying activities and social support to reactivate participation; outlining consequences for continuing and discontinuing the program). Additionally, the participants are prompted to share additional health goals and receive guidance on making them specific, measurable, attainable, relevant, and time-bound.

The intervention and control participants complete the same measurement procedures at the 12-week (midintervention) and the 24-week (postintervention) time points. There is no physiological data collection at the 36-week follow-up, as the aim to be addressed is sustaining physical activity behavior.

Participants receive up to US $830 for completing the measures per assessment period, including baseline as well as 12-, 24-, and 36-week assessments, and 12- and 24-week interviews. Semistructured exit interviews are conducted at the 24-week assessment for the first 30 participants to identify opportunities for intervention improvement and refinement.

### Data Analyses

All data will be exported into and analyzed using SAS software (version 9.4 or later). Statistical tests will be 2-sided and will be performed using a significance level of 5%. Data analyses will follow intent-to-treat principles. Data will be initially examined for variations, outliers, errors, and patterns of missing values. Missing data will be inputted using multiple imputation techniques where necessary based on the assumption that the missingness mechanism is at random. Descriptive statistics, such as means, SDs, frequencies, and proportions, will be obtained for this study’s variables.

### Primary and Secondary Aims

We will analyze between-group differences (differences between the intervention and control groups) and within-group changes from preintervention to the 12-week midintervention (immediate effects of the intervention) time point. “Clinically significant improvement” was defined for each risk factor based on the minimum change deemed clinically important; for our purposes, “clinically significant improvement” equates to the following: approximately 10% decrease in total cholesterol, 30% reduction in triglycerides, and 5% reduction in body fat from the beginning of care to the most recent measure.

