### Aims and Design of this Study

This study’s design includes three aims. The primary aim examines the immediate effect of a 24-week, synchronous M2M-C training protocol compared to a 24-week, asynchronous activity control on core indicators of CMH among 132 adult wheelchair users with ≥2 cardiometabolic risk factors. The secondary aim examines the immediate effect of M2M-C training compared to the active control condition on cardiovascular capacity, physical activity, and quality of life. The first tertiary aim evaluates the sustained effects of M2M-C training (24 to 36 wk) on physical activity participation. A second tertiary aim evaluates the potential response heterogeneity in CMH, cardiovascular capacity, and physical activity outcomes using prespecified moderator variables (eg, age, sex, body composition, diet, or ethnicity) to understand for whom the intervention is most effective.

This study’s aims will be tested using a parallel-group, assessor-blinded RCT design. For primary and secondary aims, we hypothesize that a telehealth M2M-C program will lead to significantly greater improvements in CMH outcomes, peak oxygen consumption (VO_2peak_), physical activity level, and quality of life from baseline to 24 weeks compared to controls. For the tertiary aim 1, we hypothesize that M2M-C participants will maintain physical activity levels from week 24 to week 36.

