### Outcomes

Outcomes are assessed at baseline, midintervention (12 wk), postintervention (24 wk), and follow-up (36 wk) time points. Physiological outcomes are assessed by anonymous-to-treatment assessors. The assessors are not involved in random assignment or the intervention delivery and do not directly communicate with the M2M instructors and assistant health coaches about participants. Data collection with physiological outcomes is conducted at a local research facility affiliated with a major medical center. Self-reported outcomes are administrated via a secure electronic database, referred to as REDCap. Online platform analytics are used to assess heart rate (HR) and video minutes viewed and stored in the cloud. Figure 1 shows the schedule of assessments.

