### Intervention Arm—Home-Based, Synchronous Aerobic Exercise Training Using M2M

The prescriptive exercise guideline in this proposed study was generated through a critical review of the relevant literature. To determine an appropriate exercise dose, we used data from 16 studies of moderate-intensity aerobic exercise included in a recent meta-analysis on CMH effects of exercise training in the general population [22]. Specifically, we calculated the total prescription (average prescription per week × intervention duration) for each study and the overall average. We determined that an aerobic exercise training dose of approximately 2400 minutes (40 h) over 6 months would be necessary for CMH benefits. We then spread the minutes across a 24-week intervention period for this trial with wheelchair users to ensure adequate time to safely and progressively reach the prescribed dose. The session structure and exercise minutes for each week are presented in Table 1, and the intervention components are summarized in Table 2.

**Table 1 table1:** Movement-to-music cardiovascular session structure and exercise in minutes for each week.

Week	1	2	3	4	5	6	7	8	9	10	11-24
Checking in	5	5	3	3	3	3	3	3	2	2	2
Range of motion	5	5	5	5	5	5	5	5	5	5	5
Aerobic	15	15	20	20	25	25	30	30	35	35	40
Cool down	5	5	5	5	5	5	5	5	5	5	5
End discussion	5	5	5	5	5	5	5	5	3	3	3
Exercise min/session	25	25	30	30	35	35	40	40	45	45	50
Total min/session	40	40	45	45	50	50	55	55	60	60	60

**Table 2 table2:** Summary of movement-to-music cardiovascular program features.

Feature			Description
**Prescription**			2400 minutes of exercise across 24 weeks Progressive Individualized
**Frequency**			3 times per week
**Session duration**			25 to 50 minutes
**Intensity**			Moderate-to-vigorous Maximum heart rate at or above 70% Rate of perceived exertion between 3 and 7
**Intervention length**			24 weeks
**Setting**			Home
**Exercise mode**			Aerobic using M2M^a^

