## Discussion

### Principal Findings

The CHIME study proposes a parallel-group RCT for examining the 24-week effects of an evidence-based M2M program compared with a control condition for yielding immediate and sustained CMH outcomes among adult wheelchair users with poor cardiometabolic profiles. This study anticipates that after 24 weeks, participants in the M2M-C intervention group will show significant improvements in key cardiometabolic risk factors, such as reduced HbA_1c_ levels; lower fasting glucose and triglycerides; and decreased BP, waist circumference, and body fat percentage, compared to the control group. Furthermore, the M2M-C intervention is expected to improve health-related physical fitness, including measurements such as VO_2peak_, FEV1, FVC, and grip strength, in line with self-reported psychosocial health outcomes. In addition to the improvements in CMH and physical fitness, we anticipate that these benefits will be sustained during the maintenance phase (up to 36 wk). This suggests that wheelchair users may be able to adhere to telehealth-based exercise programs over the long term. If successful, this study will be the largest and sufficiently powered confirmatory RCT trial targeting CMH outcomes in this population. The prescribed exercise dose was informed by the review of the relevant literature [22]. If successful, this study will establish an evidence-based recommendation of adequate exercise dosing for adult wheelchair users with poor CMH profiles.

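### The analysis text sets the primary and secondary comparison at week 12, while the aim, hypothesis and Discussion set it at week 24, and the sustained-effect window is shifted early in the same way

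*Protocol article*

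**What the plan says.** Four parts of the protocol article bear on timing.

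- **Aims and Design of this Study.** "The primary aim examines the immediate effect of a 24-week, synchronous M2M-C training protocol compared to a 24-week, asynchronous activity control". The hypothesis for the primary and secondary aims is greater improvement "from baseline to 24 weeks compared to controls". The first tertiary aim defines sustained effects as weeks 24 to 36 and concerns physical activity participation.
- **Outcomes.** "Outcomes are assessed at baseline, midintervention (12 wk), postintervention (24 wk), and follow-up (36 wk) time points". Week 12 is therefore the middle of the intervention and week 24 its end.
- **Data Analyses, Primary and Secondary Aims.** The analysis covers between-group differences and "within-group changes from preintervention to the 12-week midintervention (immediate effects of the intervention) time point". The same paragraph defines clinically significant improvement by percentage changes, ending with "5% reduction in body fat from the beginning of care to the most recent measure".
- **Data Analyses, Tertiary Aims.** The first sentence limits the analysis to within-group change through weeks 12 and 24 and calls week 24 the sustained effect. The next sentences apply a repeated-measures mixed model to all three aims, with between-group, within-group and group-by-time effects and Tukey-Kramer pairwise comparisons.

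The Discussion (Principal Findings) returns to the later visit: "This study anticipates that after 24 weeks, participants in the M2M-C intervention group will show significant improvements in key cardiometabolic risk factors", in comparison with the control group.

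**The concern.** The word immediate means week 24 in the aims and week 12 in the analysis. The word sustained means weeks 24 to 36 in the aims and week 24 in the analysis. Both labels sit one visit too early in the analysis text.

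The visit at which the arms are compared is part of what the trial estimates. A week-12 comparison measures the effect of a programme that is half over in time, less than half delivered in prescribed minutes, and only just at its full session length. The intervention section itself says that "an aerobic exercise training dose of approximately 2400 minutes (40 h) over 6 months would be necessary for CMH benefits", so by the article's own rationale week 12 is an early point at which to judge the primary outcomes. With one visit named in the hypothesis and another in the analysis, either could later be presented as the planned one, and the choice could be made after the data are seen.

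**Working it through.** **1. Time points side by side**

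| Item | Aims and Discussion | Analysis text |
|---|---|---|
| Primary and secondary comparison | Baseline to week 24, against control | Baseline to week 12, between and within groups |
| Immediate effect | End of the 24-week programme | Week 12, midintervention |
| Sustained effect | Weeks 24 to 36, physical activity | Through week 24, within groups only |
| Week 36 | End of the sustained window | Not mentioned |

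**2. Prescribed aerobic dose by each visit**

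Inputs: the aerobic row of Table 1 (15, 20, 25, 30 and 35 minutes per session, each for two weeks over weeks 1 to 10, then 40 minutes in weeks 11 to 24) and three sessions per week (Table 2).

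- Through week 24: 3 × [2 × (15 + 20 + 25 + 30 + 35) + 14 × 40] = 3 × (250 + 560) = 2430 minutes. The stated dose is about 2400, and 2430/2400 = 1.0125, so the article's own figure is reproduced to within 1.3%.
- Through week 12: 3 × (250 + 2 × 40) = 3 × 330 = 990 minutes.
- Share: 990/2430 = 40.7%, or 990/2400 = 41.3% on the rounded total.
- Counting range of motion and cool-down as well (Table 1, exercise minutes per session): 3 × (350 + 100) = 1350 of 3 × (350 + 700) = 3150, or 42.9%.

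The 40-minute aerobic level starts in week 11, so it has been in place for only two weeks by the end of week 12.

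**3. Does the choice of visit affect the sample size?**

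The power section gives 50 completers per group, two-sided alpha 0.05, and SDs of 43 mg/dL (total cholesterol), 4.3% (body fat) and 22.4 mg/dL (triglycerides). Exact noncentral-t power for the stated differences is:

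- 24.4/43 = 0.567: 80.2%
- 2.5/4.3 = 0.581: 82.1%
- 12.7/22.4 = 0.567: 80.1%

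The detectable standardised difference at 80% power is 0.566, as stated. The power section names no visit, so setting the contrast at week 24 changes none of these figures.

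**The case against.** The strongest reply is that the planned model already covers week 24. Under Tertiary Aims, only the opening sentence is restricted to within-group change. The model that follows is for all three aims and includes group-by-time and pairwise comparisons, and cardiometabolic measures are taken at week 24. A reader might infer that no between-group week-24 test is planned at all. The documents do not support that, because the contrast can be obtained from the stated model. What stands is narrower: no sentence designates it, and the one sentence that gives the primary and secondary aims a visit gives week 12.

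A second reply is that the article is built around a 24-week programme throughout, so the analysis text is probably a drafting slip. That is plausible, and it means the 41% should not be read as a deliberate decision to test early. But both labels are shifted consistently, so a reader cannot dismiss the text as one mistyped number. Nor is this detail left to a separate analysis plan: the article states a visit, and it contradicts the article's own hypothesis.

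A third inference concerns the improvement definition. A reader might take its end point, the most recent measure, as a last-observation-carried-forward responder rule that conflicts with intent-to-treat, and might apply the 23% attrition to 132 participants (0.23 × 132 ≈ 30) to count those affected. Neither step is supported. The paragraph defines a size of change and specifies no responder analysis or dropout rule, and the phrase may simply mean the visit being analysed. Multiple imputation is stated generally, and nothing exempts this definition. The 23% refers to completing a study that runs to week 36, and the Limitations expect some loss in weeks 25 to 36. Because no physiological data are collected at week 36, someone lost after week 24 could still have the week-24 measure. The phrase is ambiguous, and nothing stronger follows.

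**Conclusion.** The plan is wrong as written. The primary and secondary between-group analysis is tied to week 12, in conflict with the aim, the hypothesis and the Discussion, all of which use week 24. The sustained-effect analysis is tied to week 24, in conflict with the tertiary aim's weeks 24 to 36. Its within-group form suits the tertiary hypothesis that M2M-C participants maintain their activity, but it is attached to the wrong window.

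Followed literally, the main question would be assessed when 990 of 2430 prescribed aerobic minutes, about 41%, are scheduled to have been delivered. That figure assumes Table 1 is followed at three sessions per week. It is prescribed dose, not dose received, and does not measure how much smaller the effect at week 12 would be. The contradiction alone justifies correction. The loose end point of the improvement definition is a minor ambiguity to settle at the same time, and the sample-size figures stand.

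**What to change.** 1. **Primary and Secondary Aims (Data Analyses).** Replace the time-point sentence with wording such as: *The primary and secondary contrast is the between-group difference in change from baseline to week 24, estimated from the planned repeated-measures mixed model. Week-12 contrasts are supportive.*
2. **Tertiary Aims (Data Analyses).** State that the sustained-effect analysis concerns physical activity from week 24 to week 36, matching the first tertiary aim, and stop calling week 24 the sustained effect. Move the sentence introducing the mixed model for all aims out from under the tertiary heading, so that its scope is plain.
3. **Improvement definition.** Replace the open-ended end point with week 24, with missing week-24 values handled under the multiple imputation already stated.

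The cost is wording only, plus whatever amendment the change requires. Week-24 measurements and the week-36 assessment are already scheduled, and no new data or participants are needed. With 16 participants recruited by 20 August 2024 and data collection expected to run to November 2027, there was ample time at that stage to make the correction before any outcome analysis.

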We will consider the suggested outcomes as potential moderators and test effect modification by including appropriate interaction terms in our repeated measure of mixed models, including the severity of motor impairment (ie, PROMIS Physical Function 12a), clinical diagnosis (eg, SCI vs multiple sclerosis vs stroke), psychosocial metrics specific to readiness to change (eg, self-efficacy and goal setting skills), and other factors, such as wheelchair use status (full-time vs part-time), medication (use vs nonuse), and diet quality (healthy diet vs less healthy diet).

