### Rationale for Telehealth Exercise Program

A telehealth exercise program was developed to overcome the barriers of participation in exercise requiring individuals to leave their homes and use expensive equipment. This study uses an exercise program that includes various movement patterns that are coupled with elements of music and imagery, referred to as movement to music (M2M) [17]. The M2M program uses a range of different muscle groups allowing for a safer form of exercise than arm ergometry. Moreover, M2M incorporates a theory-driven telehealth delivery protocol that removes the most common barriers to participation in community and clinical exercise training studies (ie, cost, transportation, and time) [18,19]. The design of the movement-to-music cardiovascular (M2M-C) intervention is based on four key elements of social cognitive theory: self-efficacy, self-regulation, outcome expectations, and social support. These components are essential for promoting positive health behavior change. To effectively integrate these principles, the M2M-C program provides a structured, individualized, and progressively challenging exercise routine. Participants receive regular feedback and personalized guidance from M2M-C instructors and telecoaches, which helps build confidence and maintain motivation. In addition, the incorporation of music enhances movement quality and motor coordination [20] while serving as a powerful motivational tool [21]. By increasing enjoyment and improving mood, music makes exercise more appealing and engaging. This approach is consistent with the broader goal of promoting sustained physical activity among wheelchair users by addressing both psychological and physical barriers to exercise adherence.

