
### Moderating Outcome Measures

The moderating outcome measures are as follows:

Demographics and clinical characteristics of participants (eg, age, sex, ethnicity, diagnosis, or medications)Exercise behavior measured by Exercise Self-efficacy Scale [45,46], and Exercise Goal Setting and Planning Scale [47] based on Social Cognitive Theory constructsSelf-reported diet using the Rapid Eating Assessment for Participants Shortened Version [48,49]Exercise enjoyment using the Physical Activity Enjoyment Scale [50] and satisfaction via qualitative, semistructured one-on-one interviewExercise session duration based on attendance rate and video minutes viewed via online platform analyticsExercise intensity based on minutes exercised at moderate-to-vigorous intensity using an optical HR monitor (Polar Verity Sense, Polar) and RPE scale 0-10: The RPE is periodically asked during the exercise session to adjust the intensity and at the end of the exercise session to obtain the overall exertion level. The talk test is used as a secondary measure, primarily to ensure that participants stay in the moderate-to-vigorous intensity training zone and that RPE is related to aerobic strain as opposed to anaerobic. Additionally, this is an important indicator of exercise intensity, especially for individuals with a blunted exercise HR response.

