**Meeting with the instructor or coach**			
	Weeks 1-8	1× M2M instructors 2× assistant telecoaches	
	Weeks 9-16	1× M2M instructors 1× assistant telecoaches 1× self-guided with no supervision	
	Weeks 17-24	1× assistant telecoaches 2× self-guided with no supervision	
**Equipment provided**			Computer tablets Tablet stand Polar heart rate monitor
**Intervention safety**			Zoom oversight Adverse event or serious adverse event reporting

^a^M2M: movement to music.

During the 24-week training phase, the M2M-C group receives 1:1 synchronous training from M2M-trained exercise instructors and assistant health coaches within a remotely coached, home-based setting using telehealth monitoring platforms (ie, Zoom, TeleRehab app). The intervention is administered 3 times per week, starting at 25 minutes per session and increasing by 5 minutes every 2 weeks to a maximum of 50 minutes. The exercise program focuses on improving cardiorespiratory fitness using a series of movement patterns accompanied by music. The program is tailored to an individual’s functional abilities (eg, use lower limb if able, slow vs fast tempo, level of trunk control) and preference of musical themes, including classical, country, decades (oldies), international, jazz or blues, and pop.

For the first 8 weeks of the training phase, participants attend 1 instructional session with an M2M instructor per week, and the live session is video-recorded via Zoom. Participants attend 2 monitoring sessions in the same week to repeat the exercise using the prerecorded video of the week with assistant telecoaches. For the second 8 weeks (wk 9-16), participants continue to attend 1 instructional session with an M2M instructor per week, and the live sessions are video recorded. Participants attend 1 monitoring session with assistant telecoaches and 1 self-guided session without any supervision. For the third 8 weeks (wk 17-24), participants no longer meet with M2M instructors. Using the recorded videos between weeks 11 and 16 (ie, 40 minutes per video; archived with no instructions), participants attend 1 monitoring session per week with assistant telecoaches and 2 self-guided sessions in the same week.

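### Attendance, session intensity and interview satisfaction are listed as moderators although they arise after randomisation, so an arm-by-variable interaction cannot show for whom the programme works

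*Protocol article*

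**What the plan says.** Three places in the protocol article bear on this.

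- **Aims and Design of this Study.** The second tertiary aim is to study variation in response using prespecified moderators, in order to learn who gains most. The examples are baseline in character: age, sex, body composition, diet and ethnicity.
- **Moderating Outcome Measures.** The section opens "The moderating outcome measures are as follows". Its list mixes demographics, diagnosis, medication, self-efficacy, goal setting and diet with session duration (from attendance and video minutes), exercise intensity (from a heart-rate sensor and perceived exertion), and "Exercise enjoyment using the Physical Activity Enjoyment Scale" together with satisfaction by interview.
- **Data Analyses, end of Tertiary Aims.** "We will consider the suggested outcomes as potential moderators and test effect modification by including appropriate interaction terms" in the repeated-measures mixed models. The sentence goes on to name motor impairment (PROMIS Physical Function), diagnosis, self-efficacy and goal setting, wheelchair use, medication and diet quality. It gives no measurement time for any of them.

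On timing, Random Assignment places allocation after all baseline assessments. Procedure refers to interviews at 12 and 24 weeks and limits the 24-week exit interviews to the first 30 participants.

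On equipment, Table 2 lists for the M2M-C programme "Computer tablets Tablet stand Polar heart rate monitor". Procedure says control participants receive a tablet giving access to their videos.

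**The concern.** A moderator in a randomised comparison is a characteristic fixed before allocation. Each level of it then contains a randomised comparison, and the arm-by-moderator term compares those effects. Attendance, minutes at intensity and satisfaction with the programme do not have this property. They are responses to the arm received, and they also reflect motivation and health, which may affect cardiometabolic outcomes directly.

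A high attender in M2M-C and a control participant with a similar figure are not exchangeable. An interaction built on such a variable mixes three things: what the programme does, who chooses to comply, and how the variable is recorded in each arm. The question of who benefits would be answered with a description of who adhered. A positive result could then be carried into recommendations about whom to offer the programme to, or at what dose, without randomised support.

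**Working it through.** The article gives no figure for the moderator analysis, so there is none to reproduce. Its only design figure is a detectable d of 0.566 with 50 completers per group. The noncentral t distribution gives 0.5659 at 80% power, which agrees. The checks below use the same 50 per arm.

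**1. When each listed variable exists, and in which arm**

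| Listed as moderator | Exists at baseline? | Recorded in control? |
|---|---|---|
| Demographics, diagnosis, medication | Yes | Yes |
| Self-efficacy, goal setting, diet | Can be; time not stated | Not restricted by arm |
| Enjoyment scale | Time not visible (schedule figure not shown) | Not stated |
| Satisfaction by interview | No (12 and 24 weeks) | Not stated |
| Attendance | No | No coached sessions to attend |
| Video minutes | No | Open: the Outcomes section names no arm |
| Intensity by heart rate or perceived exertion | No | Sensor listed for M2M-C only; control sessions are unsupervised |

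The exit interviews cover 30 of 132 planned participants (30/132 = 23%), so exit-interview satisfaction could not serve as a trial-wide moderator in any case.

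**2. Exposure depends on arm by design.** Table 1 gives aerobic minutes of 3 × [2 × (15 + 20 + 25 + 30 + 35) + 14 × 40] = 3 × (250 + 560) = 2430 over 24 weeks, with 40 minutes per session from week 11. The control library holds 5 + 2 × 10 = 25 minutes of aerobic video in total. Those videos can be replayed, but the two arms are not offered the same exposure.

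**3. Estimability if a variable M exists in one arm only.** The model has columns [1, A, M, A×M], where A is arm. With M set to zero in control, M and A×M are the same column, so the rank is 3 of 4. If M is instead missing in control, the control rows drop out and A is constant. Neither form yields an arm-by-M interaction.

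**4. Bias if M exists in both arms.** All coefficients here are assumed; none is in the article. Let U be an unmeasured common cause and e, e′ independent standard normal errors. The outcome is Y = 0.5U + √0.75·e′, which has SD 1, no arm effect and no effect modification. Y is regressed on A, centred M and A×M in 4,000 simulated trials.

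- *Baseline M* = 0.6U + 0.8e. Mean arm term −0.004; rejection 4.8% (arm) and 5.2% (interaction).
- *Post-randomisation M* = 0.5A + 0.6U + 0.8e. The slope of Y on M within arm is (0.5 × 0.6)/(0.36 + 0.64) = 0.30, so the arm term should be −0.5 × 0.30 = −0.15. Simulated: −0.15, rejection 11.9% (arm) and 5.2% (interaction). By the same formula the bias is 0 if the arm does not shift M, and −0.30 if it shifts M by 1.0.
- *U acts more strongly on M in M2M-C:* M = 0.5A + (0.1 + 0.6A)U + 0.7e. The slopes are 0.05/0.50 = 0.10 in control and 0.35/0.98 = 0.357 in M2M-C, so a spurious interaction of 0.357 − 0.10 = 0.26 is expected. Simulated: 0.26, rejection 19.8% (interaction); arm term −0.11, rejection 8.7%.

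The interaction test is therefore not always distorted. It is distorted when the variable relates to motivation differently in the two arms. That is plausible when one arm is coached and the other is given a playlist, but the article cannot settle it.

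**The case against.** The strongest reply is that the analysis sentence itself names only variables that can be measured at baseline. Attendance, intensity and enjoyment enter only if its reference to the suggested outcomes points back to Moderating Outcome Measures. The two lists do not coincide: PROMIS Physical Function and wheelchair use appear only in the analysis text. The stated examples in the aims are also baseline in character. This stands as a reason to rest the point on Moderating Outcome Measures. It does not remove it, because that section is the one that defines a moderator set, and the analysis sentence introduces its own names as inclusions, not as a closed list.

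Other parts of the reply stand in full:

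- A reader might infer that follow-up self-efficacy or diet will be the moderator, since the programme is built on "four key elements of social cognitive theory: self-efficacy, self-regulation, outcome expectations, and social support" and the models are repeated-measures. No text selects follow-up values. A questionnaire packet is sent before the baseline visit, and the analysis text describes self-efficacy and goal setting as markers of readiness to change. Only the time point is open.
- A baseline value of PROMIS Physical Function is a legitimate moderator even though the scale is also a secondary outcome.
- One-arm recording is an inference. Table 2 summarises M2M-C alone, so it would not list control equipment. The inference is strong for the heart-rate sensor and attendance, and open for video minutes.
- An adherence analysis already exists in Tertiary Aims: proportions with exact 95% confidence intervals, overall and by subgroup.

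**Conclusion.** The point holds for attendance and video minutes, session intensity, and satisfaction by interview. The article classes them as moderators and, read with its analysis text, would test them by interaction. They follow randomisation and depend on arm, so the result would not answer the second tertiary aim. For heart-rate intensity and attendance the interaction is not estimable if control data are absent, which the article suggests without saying.

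The reach is limited. A reader might infer that the randomised arm effect as a whole is compromised. The article does not support that: nothing puts these terms into the primary or secondary comparisons, and the harm is confined to one tertiary aim. Nor can a size be fixed. The assumed scenarios give arm-term biases of −0.11 to −0.15 SD and interaction error rates of 5.2% to 19.8%, and these move with coefficients that the article does not supply. They show that the problem can be material, not how large it will be here. It is worth correcting, but it is not a threat to the main result.

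**What to change.** In Moderating Outcome Measures and at the end of Tertiary Aims, state that moderators are baseline values only: demographics, diagnosis, wheelchair use, and baseline medication, self-efficacy, goal setting, diet and PROMIS Physical Function, together with the baseline body composition named in the aims.

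Relabel attendance, video minutes, intensity, and on-programme enjoyment or satisfaction as adherence or process measures. Describe them within arm, alongside the adherence analysis already planned, or analyse them as mediators with the assumptions stated. Run no arm-interaction test on them. State in which arm heart rate, attendance and video minutes are recorded.

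The cost is a change of wording and analysis labels, with no new data and no change in sample size. The article reports 16 participants recruited by August 2024 and data collection to November 2027, so on that timetable the change can be made well before data collection ends.
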